### Data collection

All patient data are collected using the electronic data software Castor EDC (Electronic Data Capture). This software allows built-in logical checks and validations to promote data quality. Data entry and group allocation is performed by the study coordinator or locally by trained physicians and research nurses under supervision of the local investigator.

### Data analysis

All analyses will be according the intention to treat principle, restricted to eligible patients. Patients initially registered but considered ineligible afterwards based on the histological analysis on tissue extracted during surgery, will be excluded from all analyses.

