### Inclusion criteria

In order to be eligible to participate in this study, a subject must meet all of the following criteria:

Age ≥18 years and ≤90 years.Tumour diagnosed as HGG (WHO grade III/IV) on MRI as assessed by the neurosurgeon.Tumours situated in or near eloquent areas; motor cortex, sensory cortex, subcortical pyramidal tract, speech areas or visual areas as indicated on MRI (Sawaya grading II and II).^19^The tumour is suitable for resection (according to neurosurgeon).Written informed consent.

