#### Secondary outcome measures

The secondary outcomes are (1) PFS at 12 months defined as time from diagnosis to disease progression (occurrence of a new tumour lesions with a volume greater than 0.175 cm^3^, or an increase in residual tumour volume of more than 25%) or death, whichever comes first; (2) OS at 12 months defined as time from diagnosis to death from any cause; (3) oncofunctional outcome defined as the calculated coordinate of the extent of resection (or residual volume) on the x-axis and the postoperative NIHSS deterioration (delta NIHSS) on the y-axis and (4) frequency and severity of serious adverse events (SAEs) in each arm.

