### Secondary study parameters

The Kaplan-Meier method will be used to estimate PFS and OS proportions per treatment group at appropriate time points, while the Greenwood estimate of the SE (standard error) will be used to construct the corresponding 95% CI. Multivariate cox proportional hazards models will be built for PFS and OS where treatment group effect will be corrected for minimisation factors age group (≤55 years vs >55 years), KPS (80–90 vs >90) and left or right hemisphere. Additionally, competing risk analysis will be used to calculate cumulative incidence of PFS (with competing risks progression/relapse and death without progression/relapse which add up to 100% at every time point). Oncofunctional outcome will be evaluated using a scatter or bubble plot with volumetric data on the x-axis and neurological status (NIHSS) or patient performance (KPS) on the y-axis. SAEs in both groups will be described.

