### Adverse events and SAEs

AEs (adverse events) are defined as any undesirable experience occurring to a subject during the study, whether or not considered related to neurosurgery. All AEs reported spontaneously by the subject or observed by the investigator or his staff will be recorded from start of surgery until 6 weeks after surgery. SAEs (serious adverse events) are any untoward medical occurrence or effect that results in death; is life-threatening (at the time of the event); requires hospitalisation or prolongation of existing inpatients’ hospitalisation; results in persistent or significant disability or incapacity or any other important medical event that did not result in any of the outcomes listed above due to medical or surgical intervention, but could have been based on appropriate judgement by the investigator. An elective hospital admission will not be considered as an SAE. Most of the (serious) adverse effects of treatments be mainly related to the surgery: post operative pain, nausea and anaemia (in case of massive blood loss), Infections, intracranial haemorrhage, epilepsy, aphasia, paresis/paralysis in arms or/and legs.

Most of the (serious) adverse effects of treatments (awake surgery or surgery under generalised anaesthesia) will be mainly related to the surgery: postoperative pain, nausea and anaemia (in case of massive blood loss), infections, intracranial haemorrhage, epilepsy, aphasia, paresis/paralysis in arms or/and legs. The neurological morbidity is under investigation in this trial and well-known risk/complications of the craniotomy and can be attributed to the nature of the operation. Neurosurgical clinics are well adapted to prevent and treat such events. SAEs will be collected through routine data management.

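### Patients found ineligible on surgical histology are left out of every analysis, with no safety exception, so operated patients drop out of the per-arm description of serious adverse events

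*Protocol article*

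**What the plan says.** Five parts of the protocol article bear on this.

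- **Data analysis** sets the population: "All analyses will be according the intention to treat principle, restricted to eligible patients". The next sentence removes one group after surgery: "Patients initially registered but considered ineligible afterwards based on the histological analysis on tissue extracted during surgery, will be excluded from all analyses".
- **Inclusion criteria** define the tumour before any tissue is available: "Tumour diagnosed as HGG (WHO grade III/IV) on MRI as assessed by the neurosurgeon".
- **Secondary outcome measures** list, as the fourth secondary outcome, "frequency and severity of serious adverse events (SAEs) in each arm".
- **Secondary study parameters** give the whole SAE analysis in one sentence: "SAEs in both groups will be described". No separate population is named for it.
- **Adverse events and SAEs** says that adverse events "will be recorded from start of surgery until 6 weeks after surgery" and that "SAEs will be collected through routine data management". Neither statement is limited to patients with confirmed histology.

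Histology itself is entered on the 6-week follow-up form (Study procedures).

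**The concern.** Histological ineligibility can be established only from tissue taken at the operation, so everyone removed on this ground has already been through craniotomy in one of the three arms. The article describes the expected adverse effects as mostly surgical (bleeding, infection, epilepsy, aphasia, paresis). A patient runs those risks whatever the pathologist later reports.

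Restricting tumour outcomes to confirmed high-grade glioma is reasonable, because residual tumour, progression and survival mean something different in another disease. That reasoning does not carry over to SAEs. The technique is chosen on imaging, so the safety question is what happens to patients operated on for an MRI diagnosis of high-grade glioma. An SAE table limited to confirmed cases describes a group that cannot be identified when the choice is made.

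At stake is the completeness of a listed safety outcome. The same rule also removes these patients from NIHSS deterioration, the other measure of harm.

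**Working it through.** **1. Does the rule reach SAEs?** The exclusion covers all analyses. The SAE description is a planned analysis of a listed outcome. No section of the article defines an all-operated or safety population. Read as written, the rule applies to SAEs.

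**2. Were these patients exposed, and are their data available?** Entry rests on MRI, and the tissue comes from the study operation. Adverse events are recorded from the start of surgery to 6 weeks, and histology is entered on the 6-week form. The patients were exposed, and their harm data should be in the database by the time the exclusion takes effect.

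**3. How many could be affected?** Inputs from Sample size: 411 evaluable patients (137 per arm), a 10% allowance for ineligibility and withdrawal of consent combined, and 453 enrolled (151 per arm).

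- Reproducing the plan's figure: 137 × 1.10 = 150.7, rounded up to 151 per arm; 151 × 3 = 453. In total, 411 × 1.10 = 452.1, which also becomes 453 in equal arms.
- Planned allowance: 453 − 411 = 42 patients, or 151 − 137 = 14 per arm; 42 / 453 = 9.3% of those enrolled.
- The 10% is applied to 411. Taking 10% of 453 (45.3) applies it to a total already inflated and overstates the allowance.

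The 42 is a ceiling on what the plan expects. It includes patients who withdraw consent, whom this rule does not concern, and the article does not split the two.

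**4. What might that mean in SAEs?** The article gives neither the histology share nor an SAE rate, so this range rests on assumptions. Suppose 2% to 9.3% of the 453 are excluded on histology, and 10% to 30% of those have an SAE.

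- Low end: 453 × 0.02 = 9.1 patients; 9.1 × 0.10 = 0.9, about 1 patient with an SAE.
- High end: 42 patients; 42 × 0.30 = 12.6, about 13 patients with an SAE.

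**5. Why look at NIHSS as well?** Sample size assumes 3% deterioration in a mapping arm: 137 × 0.03 = 4.1 expected events. One deterioration among the excluded patients of such an arm would equal 1 / 4.1, about a quarter of that count. That is enough to justify checking whether the result holds in all operated patients.

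**The case against.** The best defence is that this is a disclosed and coherent population. The study concerns high-grade glioma, tumour type is fixed before surgery, and the sample size is stated for eligible and evaluable patients. The SAE analysis is descriptive, so no test or estimate is biased, and neurological harm is covered by a primary endpoint. All of this stands for the primary endpoints, PFS, OS and the oncofunctional outcome. It does not explain why an operated patient's SAE should be missing from a per-arm SAE table.

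Four stronger readings are tempting, and the document does not support them.

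- *The events are deleted.* They are not. Recording continues regardless of histology, and only analysis and reporting are affected.
- *The rule contradicts intention to treat.* The article qualifies that principle in the same sentence by limiting it to eligible patients. Allocation is also not randomised, so there is no randomised balance to protect. The label is loose, but the restriction is open.
- *Exclusion would differ by arm, because the tissue obtained depends on the extent of resection.* Nothing in the article says that eligibility calls vary with resection or technique.
- *SAEs are the main safety record because there is no data safety monitoring board.* NIHSS deterioration is a primary endpoint and expresses the safety objective. A monitoring board would not set the final analysis population in any case.

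**Conclusion.** The point holds in a limited form. The article fixes a rule that, followed literally, leaves operated and exposed patients out of the SAE description for each arm. This is not a detail left to a statistical analysis plan that is not shown: a plan that kept these patients for safety would have to depart from the protocol sentence.

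The size is uncertain. At the planned rates, at most 42 patients (14 per arm) fall outside the analyses for ineligibility and withdrawal of consent combined. The part due to histology is unknown, and the range of about 1 to 13 patients with an SAE depends wholly on the assumed rates. The consequence is an incomplete descriptive safety table. No primary or inferential result is shown to be distorted.

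**What to change.** Amend the exclusion sentence in Data analysis in three parts.

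1. Keep the histology exclusion for both primary endpoints, PFS, OS and the oncofunctional outcome. Narrowing it to residual volume, PFS and OS alone would put patients without high-grade glioma into the primary NIHSS analysis and change the population for which the study was sized.
2. State that SAEs are described by arm in all operated patients who have not withdrawn consent, whatever the histology, and give the number excluded on histology in each arm.
3. Add a sensitivity analysis of NIHSS deterioration at 6 weeks in all operated, consenting patients.

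The cost is a small amount of extra analysis and completing the already planned 6-week assessment in patients whose histology makes them ineligible. The sample size and visit schedule need not change.

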### Primary study parameters

The primary endpoints will be analysed using multivariate logistic regression. Subgroup analyses for tumour grade (WHO grade III/IV), preoperative neurological morbidity, preoperative tumour volume, patient’s age (in 10-year age brackets) and tumour location/eloquence will be performed.

We will be including a stratification factor in the primary analysis model with each 10 observed events using the order of prognostic value as mentioned in the paragraph above, where the first 10 events will be used to estimate the effect of the arm. This rule will be applied in case less than 40 patients in total develop neurological deterioration. In the so constructed multivariate logistic regression model the treatment arm effect will be tested at 4% significance level. The primary analysis of proportion of patients without residual contrast-enhancing and non-contrast-enhancing tumour consist of a multivariate logistic regression, where arm effect is corrected for all minimisation factors. In this model the group effect will be tested at 1% significance level. Manual or semiautomatic segmentation will be performed on axial T1 and T2/FLAIR MRI contrast enhanced slices to measure preoperative and postoperative tumour volume. A determination of volumes will be calculated blinded for the treatment group.

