### Sample size

This study has two primary endpoints. In order to guarantee that the overall type I error rate does not exceed 5%, we apply a weighted Bonferroni correction for multiple testing. The sample size calculations that follow take that into account. For the first primary endpoint, proportion of patients with neurological deterioration at 6 weeks postsurgery, we assume a deterioration rate of 10% in the control group (arm 3: no mapping), and 3% in the experimental groups (arm 1 and 2: awake and asleep mapping). A two-sample test for proportions with continuity correction requires 411 patients (137 per arm) in total in order to detect the above-mentioned difference of 7% with 80% power at a 4% significance level. For the second primary endpoint, proportion of patients without residual contrast-enhancing tumour on postoperative MRI, we assume a success rate of 25% in the control group (arm 3: no mapping), and 50% in the experimental groups (arm 1 and 2: awake and asleep mapping). A two-sample test for proportions with continuity correction requires 188 patients (94 per arm) in total in order to detect the above-mentioned difference of 25% with 80% power at a 1% significance level. In order to power the study for both primary endpoints, we should include the larger required number of patients, that is, 411. A total of 411 eligible and evaluable patients in three arms allow the difference of 25% in proportion of patients without residual tumour to be detected with 88% power. Taking into account possible ineligibility and withdrawal of consent (we estimate this at 10%), a total of 453 patients will be included (151 patients per arm).

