### Study monitoring

No scheduled on-site monitoring visits will be performed. Local investigators will remain responsible for the fact that the rights and well-being of patients are protected, the reported trial data are accurate, complete and verifiable from source documents and the conduct of the trial is in compliance with the currently approved protocol/amendment(s), with GCP (Good Clinical Practice) and with the applicable regulatory requirement(s). Direct access to source documentation (medical records) must be allowed for the purpose of verifying that the data recorded in the CRF are consistent with the original source data. No data safety monitoring board will be installed: all interventions are care-as-usual and patients are allocated without randomisation.

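### At the planning event rates, the events-per-factor rule leaves the primary NIHSS comparison of a non-randomised study with at most one adjustment factor about 95% of the time

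*Protocol article*

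**What the plan says.** Under Primary study parameters, the Protocol article tests the arm effect on NIHSS deterioration at the 4% level in a logistic model whose covariates depend on the number of events: "We will be including a stratification factor in the primary analysis model with each 10 observed events using the order of prognostic value". The ordering is that of the preceding paragraph, which lists tumour grade, preoperative neurological morbidity, preoperative tumour volume, age in 10-year brackets, and location/eloquence. The first ten events are set aside for the arm. The scope is then given: "This rule will be applied in case less than 40 patients in total develop neurological deterioration".

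Under Study monitoring, the article says that "all interventions are care-as-usual and patients are allocated without randomisation". The surgery case report form records the surgeon's rationale for the technique (Study procedures), and Study design keeps speech-eloquent tumours out of the asleep arm.

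Under Sample size, for 6 weeks after surgery, "we assume a deterioration rate of 10% in the control group (arm 3: no mapping), and 3% in the experimental groups".

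**The concern.** Rationing covariates by event count is tolerable where randomisation balances the arms, because adjustment then mainly buys precision. Here the technique is chosen for the patient. Baseline deficit, tumour volume, age and location/eloquence can plausibly drive both that choice and the NIHSS change. Location is tied to arm by design, yet stands last in the list. The article states no matching, weighting or propensity score for this endpoint.

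If the planned number of events admits almost no covariates, the test at 4% is close to a crude comparison of patients selected by their surgeons. The article fixes this rule for the confirmatory model itself, so it is not a detail left to a later analysis plan.

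**Working it through.** **Inputs (Sample size and Primary study parameters).** Deterioration 10% (no mapping) and 3% (each mapping arm); 137 evaluable patients per arm, 411 in total; ten events for the arm, then one factor per further ten, below 40 events.

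**The plan's own figure.** The article says that the test "requires 411 patients (137 per arm) in total" for a "difference of 7% with 80% power at a 4% significance level". Take control against the two mapping arms pooled (k = 2), one-sided 4%:
- Pooled rate = (0.10 + 2 × 0.03)/3 = 0.0533.
- n = [1.751 × √(1.5 × 0.0533 × 0.9467) + 0.842 × √(0.10 × 0.90 + 0.03 × 0.97/2)]² / 0.07² = 116 controls.
- With continuity correction, n' = (n/4) × [1 + √(1 + 2(k+1)/(n × k × 0.07))]² = 29 × [1 + √(1 + 6/16.24)]² = 136.6, so 137 controls + 274 mapped = 411.

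The figure therefore reproduces, though only one-sided and pooled (two-sided gives 164 per arm, 492 in total). That is a separate matter and does not alter the event count below.

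**Expected events.** 137 × 0.10 + 274 × 0.03 = 13.70 + 8.22 = 21.9. SD = √(137 × 0.10 × 0.90 + 274 × 0.03 × 0.97) = 4.5.

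**What the rule admits.** Exact distribution of Binomial(137, 0.10) + Binomial(274, 0.03):

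| Events | Factors besides arm | Probability |
|---|---|---|
| under 20 | none | 30.4% |
| 20–29 | one | 64.5% |
| 30–39 | two | 5.1% |
| 40 or more | rule no longer applies | 0.02% |

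At most one factor: 30.4% + 64.5% = 94.9%.

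**Sensitivity to the event rates (only the planning rates are the plan's own).**

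| Scenario | Expected events | P(at most one factor) |
|---|---|---|
| 453 patients, planning rates | 24.2 | 86.9% |
| 411, 10% v 5% v 5% | 27.4 | 67.0% |
| 411, 15% v 5% v 5% | 34.3 | 19.6% |
| 411, 10% in all arms | 41.1 | 2.4% |

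**Illustration of the bias (assumptions, not in the documents).** Simulation of 411 patients with about 22 events and no true effect. Three binary factors are left out of the model, each with odds ratio 2 on arm and 2 on outcome:

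| Direction of selection | Median OR | Rejection at nominal 4% |
|---|---|---|
| higher-risk patients less often mapped | 0.71 | 8.8% |
| higher-risk patients more often mapped | 1.44 | 4.7% |
| mixed signs | 0.89 | 3.8% |

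A rejection rate near 4% does not mean that the estimate is sound: in the second row it is still 44% too high on the odds-ratio scale.

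**The case against.** Five objections deserve weight.

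1. **The event count belongs to the design alternative.** Twenty-two events arise only if mapping works as planned. With no effect at the 10% control rate, 411 × 0.10 = 41.1 events are expected and at least two factors enter about 98% of the time. This stands. The simulation therefore needs a common rate of about 5.3% (16%/3), which the plan nowhere states, and a reader should not infer that the plan's type I error is about 9%. But a primary model should also be adequate at the alternative for which the study is sized.

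2. **The direction of confounding is unknown.** A reader might infer that the bias favours mapping. The documents do not support that: surgeons may equally map the riskier tumours. This stands, and is why a range is shown.

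3. **The factor list is loosely worded.** A reader might infer that grade is certainly the one covariate. That is the literal order, but the list is introduced for subgroup analyses, while Secondary study parameters names three minimisation factors (age group, KPS, hemisphere). Arm plus three factors at ten events each gives exactly 40. The cut-off may thus point to that other list, so it cannot be called an error for failing to match five factors. Under either list the limit of at most one covariate is the same.

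4. **The rates are for 6 weeks.** The endpoint also covers 3 and 6 months, for which no rates are given. This stands.

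5. **The article admits residual bias.** Its strengths and limitations say so in general terms. That does not justify leaving measured confounders out of the primary model. The absence of centre from the stated models is different: a condensed article may leave it to the analysis plan, and it is not part of this point.

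**Conclusion.** The point holds. At the planning rates the rule gives a primary NIHSS model with no covariate (30%), one (65%) or two (5%), in a study without randomisation. Most of the measured factors that can plausibly drive both technique and outcome would be left out, so confounding by indication stays in the primary test.

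The conclusion rests on the planning rates at 6 weeks and on counting the arm as one term. If the three-level arm is counted as two terms, 22 events leave no room for any covariate (22 − 20 = 2). It weakens as event rates rise above plan.

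The bias itself cannot be sized from the documents. The range of about 0.7 to 1.4 in the median odds ratio, with rejection of about 4% to 9%, depends on assumed odds ratios of 2. It would go too far to say that a significant result must be spurious or that the error rate is known to be inflated. What follows is that the planned model gives little basis for separating a mapping effect from patient selection.

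**What to change.** Remove the event-count gate and prespecify one confounder set, used whatever the number of events: baseline NIHSS, preoperative volume, age, KPS, location/eloquence, hemisphere and grade. All are already collected: WHO grade on the six-week form, the rest at baseline.

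Apply the set through a propensity score, either multinomial for the three arms or a separate score for each pairwise contrast. Use it as overlap weights or as a covariate in a penalised logistic model. The score is fitted to the arm sizes (137 each), so about 22 outcome events do not limit it.

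Restrict any contrast involving the asleep arm to motor-eloquent tumours. Study design excludes speech-eloquent tumours from that arm, so those patients have no counterpart there and no weighting can supply one.

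The cost is changed wording, modest extra analysis, a somewhat wider interval, and an estimate that applies to patients who could have received either technique. No new data are needed. Keeping the rule and enlarging the study instead is impractical: reaching 40 events at the average planning rate would take 40/0.0533, about 750 evaluable patients.

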**Methods and analysis:**

This study is an international, multicenter, prospective three-arm cohort study of observational nature. Consecutive HGG patients will be operated with awake mapping, asleep mapping or no mapping with a 1:1:1 ratio. Primary endpoints are: (1) proportion of patients with National Institute of Health Stroke Scale deterioration at 6 weeks, 3 months and 6 months after surgery and (2) residual tumour volume of the contrast-enhancing and non-contrast-enhancing part as assessed by a neuroradiologist on postoperative contrast MRI scans. Secondary endpoints are: (1) overall survival and (2) progression-free survival at 12 months after surgery; (3) oncofunctional outcome and (4) frequency and severity of serious adverse events in each arm. Total duration of the study is 5 years. Patient inclusion is 4 years, follow-up is 1 year.

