### Outcomes

#### Primary outcome measures

The primary outcomes are (1) proportion of patients with NIHSS deterioration at 6 weeks, 3 months and 6 months postoperatively; deterioration is defined as an increase of at least one point on the total NIHSS score compared with this score at baseline and (2) residual tumour volume of the contrast-enhancing and non-contrast enhancing part, as assessed by a neuroradiologist on postoperative T1 with contrast and T2/FLAIR MRI scan sequences using manual or semiautomatic volumetric analyses (Brainlab Elements iPlan CMF Segmentation, Brainlab AG, Munich, Germany or similar software).

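### The second primary endpoint is defined inconsistently across Outcomes, Sample size and Analysis, and its power and alpha are established for only one of the definitions

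*Protocol article*

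**What the plan says.** The protocol article describes primary endpoint 2 in four places.

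- **Abstract (Methods and analysis):** "residual tumour volume of the contrast-enhancing and non-contrast-enhancing part as assessed by a neuroradiologist on postoperative contrast MRI scans". This is a volume, covering both parts.
- **Primary outcome measures:** "residual tumour volume of the contrast-enhancing and non-contrast enhancing part, as assessed by a neuroradiologist". Again a volume of both parts, measured on contrast T1 and T2/FLAIR.
- **Sample size:** "For the second primary endpoint, proportion of patients without residual contrast-enhancing tumour on postoperative MRI". This is a yes/no outcome for the contrast-enhancing part only, with 25% assumed under no mapping and 50% under either mapping technique, tested at 1%. The closing power statement in the same section drops the compartment and speaks only of residual tumour.
- **Primary study parameters:** "The primary analysis of proportion of patients without residual contrast-enhancing and non-contrast-enhancing tumour consist of a multivariate logistic regression". This is a yes/no outcome that names both parts, with the group effect tested at 1%.

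Sample size also promises that a weighted Bonferroni correction keeps the overall type I error at or below 5%, divided as 4% for neurological deterioration and 1% for this endpoint. Study design lists evaluation of the non-contrast-enhancing part as a deliberate difference from the sister randomised trial.

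**The concern.** The definitions differ in scale (volume or yes/no) and in compartment (contrast-enhancing only, or both), and no section reconciles them. The compartment matters for individual patients. Someone whose enhancing tumour is fully removed but who has T2/FLAIR tumour left is a success in Sample size. If the analysis sentence means that neither part may remain, the same patient is a failure there.

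Two things are at stake. The assumed rates and the power may not belong to the variable that is tested. Or, if each part is tested separately, the 1% reserved for this endpoint has to cover two tests, and the document does not say how. This is not detail that an article leaves to a fuller document: the statements conflict as written, and a separate analysis plan could agree with only one of them.

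**Working it through.** **1. Reproduce the plan's own figure.** Inputs from Sample size: p1 = 0.25, p2 = 0.50, α = 0.01, power 80%, continuity correction. The number of sides is not stated; two-sided is taken here. With d = |p1 − p2|, k = ratio of experimental to control patients (k = 1), and p̄ = (p1 + k·p2)/(1 + k):

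- n = [z(1−α/2)·√(p̄(1−p̄)(1+1/k)) + z(power)·√(p1(1−p1) + p2(1−p2)/k)]² / d²
- n = [2.5758·√(0.375·0.625·2) + 0.8416·√(0.1875 + 0.25)]² / 0.25² = (1.7635 + 0.5567)² / 0.0625 = 86.1
- n with correction = (n/4)·[1 + √(1 + 2(1+1/k)/(n·d))]² = 21.53·[1 + √(1 + 4/(86.1·0.25))]² = 93.97, rounded up to 94

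This matches the stated 94 per arm (188 in total). One-sided 1% would give 82, so the plan's figure is two-sided, and it belongs to freedom from contrast-enhancing residual.

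**2. Reading A: the analysis sentence is a composite (neither part remains).** Patients free of both parts are a subset of those free of the enhancing part, so the composite rate cannot exceed the enhancing-only rate in any arm. The document gives no composite rates, so those below are assumptions. Power for m control patients inverts the formula above:

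- n* = m·[1 − (1+1/k)/(2·m·d)]²
- power = Φ{[d·√n* − z(1−α/2)·√(p̄(1−p̄)(1+1/k))] / √(p1(1−p1) + p2(1−p2)/k)}

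Example, 15% vs 30%, m = 137, k = 1: n* = 137·(1 − 1/20.55)² = 124.0. The numerator is 0.15·√124.0 − 2.5758·√(2·0.225·0.775) = 1.670 − 1.521 = 0.149. The denominator is √(0.1275 + 0.21) = 0.581. Φ(0.257) = 60%.

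| Control vs mapping | Status of rates | 137 vs 137 | 137 vs 274 (mapping arms pooled) |
|---|---|---|---|
| 25% vs 50% | stated, enhancing only | 95% | 99% |
| 20% vs 40% | assumed composite | 82% | 93% |
| 15% vs 40% | assumed composite | 98% | over 99% |
| 15% vs 30% | assumed composite | 60% | 75% |
| 10% vs 20% | assumed composite | 33% | 43% |

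The result depends on whether the 25-point difference survives (15% vs 40%) or shrinks with the rates (20% vs 40%, 15% vs 30%, 10% vs 20%). The document's own 88% for 25% vs 50% at 411 patients is not the 95% in the first row. That is a separate matter and the present point does not rest on it.

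**3. Reading B: two proportions, one per part.** Freedom from enhancing residual is then analysed as powered, and step 2 does not apply to it. The error allowance becomes 4% (deterioration) + 1% (enhancing) + 1% (non-enhancing) = 6% by the Bonferroni sum, against the guaranteed 5%. The document gives no split of the 1% and no testing order.

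**4. The volume definition.** No mean or standard deviation is given for residual volume, so no power can be calculated for it. Primary study parameters sends both primary endpoints to logistic regression, so no primary analysis of volume on its continuous scale is stated.

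**The case against.** The best defence is that volume is simply the measurement and absence of residual is its dichotomy, both taken from the same blinded segmentation. Primary study parameters fixes logistic regression, a proportion and the 1% level. This largely stands. A reader might infer that the sponsor is free to pick among three outcomes once the data are seen. The documents do not support that, because the continuous version is not left open as an analysis. What remains open is which compartment or compartments count. The volume wording in the abstract and Outcomes is still a mismatch to correct.

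A second defence is that the analysis sentence may mean two proportions, in which case the powered outcome is analysed after all. This also stands as a possible reading. A reader might infer outright that the tested variable is not the powered one and that power is lost. The first part holds only under the composite reading. The second holds only under some rates: at 20% vs 40% or 15% vs 40%, power stays above 80%. Nor can the power concern and the 6% be added together, since they belong to mutually exclusive readings.

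Neither defence removes the conflict, because each reading leaves one of the two problems in place.

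**Conclusion.** The point holds as an inconsistent and ambiguous definition of a primary endpoint. It is certain from the text that the descriptions conflict and that only freedom from contrast-enhancing residual has stated rates and a reproducible sample size.

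The consequence depends on the reading. Under the composite, the 25%/50% calculation does not transfer. With 137 per arm at two-sided 1% and one mapping arm against control, power ranges from 33% to 98% over the assumed rates. Under two separate tests at 1%, the nominal total is 6% instead of 5%. The documents do not establish which applies, so a definite loss of power cannot be claimed. Because this is a primary endpoint, the definition should be settled before analysis.

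**What to change.** Use one definition in the abstract, Primary outcome measures, Sample size (including its closing power statement) and Primary study parameters.

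The simplest choice is absence of residual contrast-enhancing tumour on postoperative MRI, tested once at 1%, because its rates and sample size already exist. The non-contrast-enhancing part can follow in one of two ways:

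- as a hierarchical test at the same 1%, carried out only if the contrast-enhancing test is significant, which keeps the 5% total; or
- as a key secondary outcome.

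Report residual volumes of both parts as continuous secondary outcomes, adjusted for the corresponding preoperative volume.

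If the sponsor prefers the composite, it should say so, state the assumed composite rates per arm and restate the power at 1%.

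The cost is more than wording. No additional measurement is needed, since both parts are already segmented. But the non-contrast-enhancing part, which Study design names as a deliberate addition, would lose co-equal primary status under the simplest option. Choosing the composite avoids that, but if the assumed rates are low the planned 411 evaluable patients may not give 80% power.
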